**Sensitivity Analysis:**
To assess the influence of significant concurrent metabolic acidosis, a sensitivity analysis of the primary outcome will be performed after excluding cases with severe metabolic acidosis (e.g., base excess <-5 mmol/L at Timepoint 2).To confirm the specific impact of significant respiratory acidosis, a second sensitivity analysis will be performed restricted to patients with PaCO₂ ≥ 50 mmHg at the intervention timepoint.

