## Introduction

Prone positioning has become an increasingly common approach for thoracoscopic esophageal cancer surgery to facilitate surgical exposure. It has been associated with better surgical outcomes and improved perioperative safety compared to the classical lateral decubitus position [1]; however, it may significantly impact ventilation. Partial lung collapse and intrathoracic insufflation of carbon dioxide (CO₂), commonly used in these procedures, may contribute to significant alterations in respiratory physiology and acid-base balance.

Clinically, elevations in serum potassium levels associated with acute respiratory acidosis are often observed during these surgeries. While acidosis is generally known to affect potassium distribution, respiratory acidosis is typically considered to cause only minimal or no elevation in serum potassium compared to metabolic acidosis [2–3]. However, recent clinical reports challenge this view in the setting of critical illness; for instance, Pathak and Nanda described cases of severe, refractory hyperkalemia in COVID-19 patients where acute respiratory acidosis was identified as a major contributing factor [4]. Nevertheless, the combination of prone positioning, ventilatory compromise, and CO₂ insufflation may alter the expected physiological response.

The primary aim of this study is to quantify the magnitude of serum potassium elevation associated with acute respiratory acidosis during prone-position esophagectomy. Furthermore, we aim to explore the physiological drivers of this phenomenon, including the respective contributions of respiratory and metabolic factors. Ultimately, this research may contribute to enhancing the safety of ventilation strategies and optimizing electrolyte management for these complex procedures.

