**Analyses of Factors Associated with Potassium Increase:**
**Correlation Analysis:** To explore potential physiological drivers, correlations between the change in serum potassium (ΔK⁺) and changes in other variables will be assessed. These variables will include the change in PaCO₂ (ΔPaCO₂) and markers of metabolic stress, such as the change in lactate (ΔLac).**Multivariable Analysis of** Δ**K** ⁺ **:** A multivariable linear regression analysis will be performed to identify factors independently associated with the magnitude of the serum potassium increase (ΔK⁺). Candidate covariates for the multivariable model include the change in PaCO₂ (ΔPaCO₂), change in lactate (ΔLactate), baseline eGFR, fluid balance, norepinephrine dose, and the duration of the prone position. The final selection of independent variables will be determined based on clinical relevance, assessment of multicollinearity (e.g., variance inflation factor), and the sufficiency of outcome events to avoid overfitting.

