**Exploratory and Clinical Analyses:**
**Risk Factors for Clinical Hyperkalemia:** As an exploratory analysis, a multivariable logistic regression will be performed to identify risk factors for the development of clinically significant hyperkalemia (defined as serum potassium > 5.0 mmol/L).**Subgroup Analysis:** Subgroup analyses will be conducted based on key clinical factors, including **preoperative renal function (e.g., stratified by eGFR categories)** and bronchial blocker usage.**Assessment of Acid-Base Components:** Changes in other acid-base parameters (e.g., HCO₃ ⁻ , BE, anion gap) will be descriptively analyzed.

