## Discussion

This study protocol was designed to address a critical clinical observation: a greater-than-expected elevation in serum potassium during prone-position esophagectomy. This finding stands in contrast to the conventional physiological understanding that respiratory acidosis—a common consequence of this procedure—causes minimal or no elevation in serum potassium, particularly when compared to metabolic acidosis [2–3]. Therefore, the primary objective of this study is first to confirm and quantify the mean increase in serum potassium between the supine (baseline) and prone-position phases. Given that acute respiratory acidosis is an almost inevitable event during this surgical phase, demonstrating a statistically significant potassium increase would, in itself, strongly suggest a clinically relevant phenomenon that challenges existing knowledge. However, we recognize that major surgery introduces multiple confounding variables that could influence potassium levels, such as metabolic stress. To address this complexity, our secondary analyses are designed to (1) assess the robustness of our primary finding via sensitivity analysis that controls for the effect of metabolic acidosis, and (2) explore the association between the potassium increase and various physiological drivers, including the severity of respiratory acidosis itself.

In particular, surgical techniques involving partial lung collapse and intrathoracic CO₂ insufflation may lead to rapid external CO₂ loading, resulting in acid-base changes distinct from those seen in endogenous respiratory acidosis. Multiple mechanisms, including H⁺/K⁺ exchange and altered ATPase activity, may contribute to this response. The body’s compensatory systems may not be able to fully respond to the acute rise in PaCO₂, potentially leading to more pronounced potassium fluctuations than typically expected.

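### The metabolic exclusion and the named regression terms leave out the change in base excess, so respiratory and metabolic contributions to the potassium rise are not adequately separated

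*Protocol article*

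**What the plan says.** The Introduction states a secondary aim of exploring physiological drivers, "including the respective contributions of respiratory and metabolic factors". Four parts of the plan bear on it.

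- **Sensitivity Analysis** (Secondary outcomes): the primary comparison is repeated "after excluding cases with severe metabolic acidosis (e.g., base excess <-5 mmol/L at Timepoint 2"). A second analysis is "restricted to patients with PaCO₂ ≥ 50 mmHg at the intervention timepoint".
- **Analyses of Factors Associated with Potassium Increase**: the correlation analysis uses the change in PaCO₂ and "markers of metabolic stress, such as the change in lactate". Besides the change in PaCO₂, the candidate regression terms are "change in lactate (ΔLactate), baseline eGFR, fluid balance, norepinephrine dose, and the duration of the prone position".
- **Exploratory and Clinical Analyses**: changes in bicarbonate, BE and anion gap "will be descriptively analyzed".
- **Data collection**: potassium, pH, PaCO₂, bicarbonate, BE, anion gap and lactate are all recorded at baseline, at the prone-phase sample and after the procedure. Where there are several prone samples, the one with the lowest pH is used.

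The Discussion presents the secondary analyses as a way to "assess the robustness of our primary finding via sensitivity analysis that controls for the effect of metabolic acidosis".

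**The concern.** The outcome is a within-patient change from Timepoint 1 to Timepoint 2. To ask whether a metabolic disturbance explains part of that change, the matching quantity is the change in BE over the same interval. The plan uses it in no inferential analysis: the exclusion rule looks only at where BE ends up, and the regression relies on lactate, which does not register acidosis without a lactate rise.

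The rule for choosing Timepoint 2 sharpens this. A low pH can come from a high PaCO₂ or from a loss of base, so taking the lowest-pH sample does not favour purely respiratory disturbances.

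At stake is the interpretation of the secondary results. If potassium still rises after the exclusion, or if the PaCO₂ coefficient is positive, readers will be invited to call the effect respiratory. A metabolic shift between the two samples could still be present in both analyses.

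**Working it through.** The article gives no BE distribution, so it has no figure of its own to reproduce on this point. The first step below is arithmetic on the stated rule. The other two are illustrations on assumed inputs.

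**1. What the exclusion rule does.** Rule: remove if BE at Timepoint 2 is below -5.

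| Patient | BE at T1 | BE at T2 | Change | Rule |
|---|---|---|---|---|
| A | +2 | -4.5 | -6.5 | kept |
| B | -4 | -5.5 | -1.5 | removed |

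Patient A has more than four times the metabolic shift of patient B (6.5/1.5 = 4.3) and stays in. The PaCO₂ ≥ 50 mmHg restriction sets no condition on BE, so it does not alter this.

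**2. How much metabolic shift survives the cut (assumed inputs).** Let baseline BE be normal with mean m_B and SD 2, and let the change in BE be independent and normal with mean m_D and SD s_D. BE at T2 then has mean m_B + m_D and SD s = √(4 + s_D²). With a = (-5 - m_B - m_D)/s, the share removed is Φ(a), and the mean change among those kept is m_D + (s_D²/s)·φ(a)/(1 - Φ(a)).

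For m_B = 0, m_D = -3, s_D = 2: s = 2.828, a = -0.707, share removed 24%, and mean change among those kept = -3 + 1.414 × 0.3107/0.760 = -2.42, which is 81% of -3.

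| m_B | m_D | s_D | Removed | Mean change, kept | Share of fall retained |
|---|---|---|---|---|---|
| 0 | -2 | 1.5 | 11% | -1.80 | 90% |
| 0 | -3 | 2 | 24% | -2.42 | 81% |
| 1 | -3 | 2 | 14% | -2.62 | 88% |
| 1 | -4 | 2 | 24% | -3.42 | 86% |
| 2 | -4 | 2 | 14% | -3.62 | 91% |

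A simulation of the same cases agrees to within rounding. In it, 20-64% of retained patients had a BE fall of at least 3 mmol/L, and 2-34% of removed patients had a smaller fall than that.

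**3. Leaving the change in BE out of the regression (assumed inputs).** Take SD of the change in PaCO₂ 12 mmHg, SD of the change in BE 2.5 mmol/L, a correlation ρ of 0.3-0.5 (in size) between the changes in lactate and BE, and no correlation between the changes in lactate and PaCO₂. Let the true effects on potassium be 0.10 mmol/L per 10 mmHg and 0.08 mmol/L per 1 mmol/L fall in BE. If the changes in PaCO₂ and BE correlate at r after lactate is allowed for, the fitted PaCO₂ slope per 10 mmHg is

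0.10 - 10 × 0.08 × r × 2.5√(1 - ρ²)/12.

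| r | ρ = 0.3 | ρ = 0.5 |
|---|---|---|
| -0.3 | 0.148 | 0.143 |
| 0 | 0.100 | 0.100 |
| +0.3 | 0.052 | 0.057 |

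Adding the change in BE to the model restores 0.10 in every row. The bias can go either way, and it vanishes when r = 0.

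**The case against.** Five points can be made for the plan.

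- **The aim is modest.** It is to explore, and the limitations paragraph admits that separating the components of a mixed disorder is difficult. A reader might infer that the aim cannot be met at all. The documents do not support that: the changes in PaCO₂ and lactate give a partial separation, and the mean change in BE will be reported.
- **The lists are open.** Metabolic markers are introduced by example, the covariates are candidates, the BE cut is itself given as an example, and a fuller analysis plan may exist. Nothing bars the change in BE. This stands, but the article does assign that change a role, and the role is description. It also says it is published to fix the analysis before data access, so a term added later would look post hoc.
- **Other covariates help.** Fluid balance and baseline eGFR are candidates and bear on fluid-related and renal acidosis. They are indirect proxies, while a direct measure is already being collected.
- **The exclusion targets severe cases only.** For that narrow purpose an absolute threshold is legitimate and worth keeping. It does not justify the Discussion's wording, which claims control of metabolic acidosis in general.
- **The bias is hypothetical.** This also stands. A reader might infer that metabolic acidosis will be credited to PaCO₂ and inflate its coefficient. The documents give neither the sign nor the size of the correlation on which that depends.

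**Conclusion.** As written, the plan does not adequately separate respiratory from metabolic contributions. Two parts of this rest on the text alone: the exclusion ignores baseline BE although the outcome is a change, and the Discussion claims more for that exclusion than it can deliver. The sizes rest on assumption. Over the BE distributions tried, 81-91% of the mean BE fall stays in the supposedly non-metabolic subset. In the regression illustration, a true slope of 0.10 mmol/L per 10 mmHg is estimated at anything from about 0.05 to 0.15, and correctly if the changes in BE and PaCO₂ are unrelated after lactate.

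The primary outcome, the mean paired difference in potassium, is untouched. The weakness lies in attributing that difference to a cause. It should be corrected before data extraction because the remedy is cheap.

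**What to change.** 1. Pre-specify the change in standard BE (Timepoint 2 minus Timepoint 1) as a term beside the change in PaCO₂ in the regression for the potassium change, and report both coefficients with confidence intervals. Lactate can stay as a secondary metabolic marker.
2. Add a sensitivity analysis defined on the fall in BE between the two timepoints, with its threshold fixed before extraction, and show it alongside the absolute -5 cut. The 3 mmol/L used in the illustration above is not a proposed threshold.
3. In the Discussion, say that the sensitivity analysis excludes severe metabolic acidosis, in place of the claim that it controls for metabolic acidosis.

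Cost: no new data, since BE at both timepoints is already on the collection list. The model gains one degree of freedom: with about 150 patients and all six named candidates, patients per term fall from 150/6 = 25 to 150/7 ≈ 21. Some collinearity with lactate is likely; the planned variance inflation check would show it, but the change in BE should stay in the model whatever that check shows.

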### Outcomes

#### Primary outcome.

The mean difference in serum potassium levels between the baseline (supine) and the intraoperative (prone) timepoints.

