### Sample size estimation

The sample size calculation is based on the study’s primary outcome: the mean difference in serum potassium levels within the prone-position cohort. Our preliminary data from 50 cases indicate that serum potassium concentration increases by a mean of 0.73 mmol/L (standard deviation [SD] 0.53) during the prone phase. While this large effect size would allow for statistical significance with a very small sample, we aimed to power the study to detect a more conservative, yet still clinically significant, difference of 0.5 mmol/L. Although the precise threshold for adverse cardiovascular effects associated with an acute potassium increase remains undefined, the relationship between serum potassium and cardiovascular events typically follows a U-shaped curve [5]. Recent evidence further suggests that the magnitude of potassium increase is a significant predictor of arrhythmias [6]. Therefore, in the clinical setting of esophagectomy, we considered a 0.5 mmol/L increase to be a clinically relevant safety margin. Assuming a paired t-test with a two-sided alpha of 0.05 and a power of 80%, a minimum of 34 patients in the prone-position cohort is required.

We plan to include all eligible patients from both institutions within the study period (January 2022 - December 2024), targeting a total sample size of approximately 150 cases. While the primary power calculation is met with 34 patients, this larger sample size will provide robust data for the secondary outcomes, including the multivariable regression analyses, ensuring greater precision and the ability to explore multiple predictor variables.

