#### Analysis for the primary outcome.

A paired t-test will be used to compare the mean serum potassium levels between the baseline and intraoperative timepoints.

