#### Analyses for secondary outcomes.

**Analyses of Factors Associated with Potassium Increase:** For correlation analysis, Pearson or Spearman correlation will be used. For multivariable analysis of ΔK ⁺ , a linear regression model will be developed.**Sensitivity Analysis:** The primary outcome will be re-analyzed using a paired t-test on the subset of patients excluding those with severe metabolic acidosis.**Exploratory and Clinical Analyses:** For identifying risk factors for clinical hyperkalemia, a multivariable logistic regression model will be used. For subgroup analyses, the primary outcome will be compared between strata (e.g., using an independent t-test or ANOVA). Other exploratory analyses will be descriptive or use appropriate statistical tests as needed.

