Beyond this specific surgical procedure, our findings hold potential implications for the management of critically ill patients in the ICU, particularly those with respiratory failure. Patients with conditions such as Acute Respiratory Distress Syndrome (ARDS) often present with comorbid cardiac or renal dysfunction, making them exceptionally vulnerable to the life-threatening consequences of hyperkalemia. Our findings may suggest that hyperacute respiratory acidosis, in particular, warrants closer monitoring of electrolyte balance than previously appreciated. This perspective may also prompt a re-evaluation of permissive hypercapnia strategies. While permissive hypercapnia is employed to protect the lungs, its potential impact on electrolyte homeostasis is not fully understood.

Our exploratory multivariable analysis, by seeking to identify predictors for the magnitude of potassium increase, may help in identifying surrogate markers to define the safe limits of hypercapnia in critically ill patients.

This study has several methodological strengths. First and foremost, the use of a paired-design, where each patient serves as their own control, is a powerful approach to minimize the influence of inter-patient variability. Second, its two-center nature increases the generalizability of our findings. Furthermore, the collection of detailed, serial arterial blood gas data allows for a granular analysis of the acute physiological changes. Finally, our pre-specified plan to conduct a sensitivity analysis demonstrates a rigorous effort to isolate the effects attributable to respiratory changes, thereby strengthening the specificity of our conclusions.

Several limitations of this study should be acknowledged. First, its retrospective design leads to inherent variability in the timing of blood gas sampling and a lack of standardized protocols. Second, our study includes only patients in whom blood gas analysis was performed, potentially introducing selection bias. However, we believe this may have selectively enriched our sample with patients exhibiting more severe respiratory compromise, which aligns with our primary research question. Finally, distinguishing the precise contributions of respiratory and metabolic components to a mixed acid-base disorder is inherently challenging.

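### The PaCO₂ ≥ 50 mmHg sensitivity analysis has no comparator, so it cannot confirm an effect specific to respiratory acidosis

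*Protocol article*

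**What the plan says.** The primary outcome is defined as "The mean difference in serum potassium levels between the baseline (supine) and the intraoperative (prone) timepoints". Its test is given under Analysis for the primary outcome: "A paired t-test will be used to compare the mean serum potassium levels between the baseline and intraoperative timepoints".

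Under Secondary outcomes, Sensitivity Analysis, the protocol plans two re-analyses of that outcome. The first drops patients with base excess below −5 mmol/L at Timepoint 2. The second carries a stated inferential purpose: "To confirm the specific impact of significant respiratory acidosis, a second sensitivity analysis will be performed restricted to patients with" PaCO₂ ≥ 50 mmHg. No group below 50 mmHg is mentioned for it.

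Under Analyses for secondary outcomes, the method is spelled out for the first re-analysis only: "The primary outcome will be re-analyzed using a paired t-test on the subset of patients excluding those with severe metabolic acidosis". The between-strata comparisons in that section belong to the subgroup analyses, and the strata named for those are renal function and bronchial blocker use, not PaCO₂.

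Elsewhere in Secondary outcomes, the change in potassium (ΔK) is to be correlated with the change in PaCO₂ (ΔPaCO₂). ΔPaCO₂ is also listed as a candidate covariate in a linear regression of ΔK, with the final choice of variables left open.

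The Discussion describes the base-excess re-analysis as a "sensitivity analysis that controls for the effect of metabolic acidosis", and says that the sensitivity plan "demonstrates a rigorous effort to isolate the effects attributable to respiratory changes".

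**The concern.** To show that PaCO₂ matters for potassium, patients with more hypercapnia must be compared with patients with less. Restricting to PaCO₂ ≥ 50 mmHg removes the less exposed patients and leaves a before/after test against zero. Elapsed time, anaesthesia, fluids or tissue trauma could each produce the same rise, and the test cannot tell them from CO₂.

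The protocol is published before data access so that the analyses are fixed in advance. If an analysis is labelled as confirmation and is almost sure to be significant whatever role PaCO₂ plays, its significance carries no information on that role. The Discussion goes on to draw implications for monitoring and for permissive hypercapnia from the respiratory explanation, so the label matters.

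**Working it through.** **Inputs.** From Sample size estimation: "serum potassium concentration increases by a mean of 0.73 mmol/L (standard deviation [SD] 0.53) during the prone phase", from 50 cases; the design difference, "a more conservative, yet still clinically significant, difference of 0.5 mmol/L"; two-sided alpha 0.05; about 150 patients planned. The share of patients with PaCO₂ ≥ 50 mmHg is not given; 30% to 90% is assumed, that is 45 to 135 of 150. The Discussion expects respiratory acidosis in nearly every case, so the high end is plausible.

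**Plan's own figure.** The protocol gives no figure for this analysis. Its only sample-size figure, 34, concerns the primary test and is not used here. (With 0.5 and SD 0.53 the paired t-test needs 11; 34 is reached with SD 1.0. That is a separate matter.)

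**Step 1: what is already known.** In the preliminary cases, t against zero = 0.73 / (0.53/√50) = 0.73 / 0.0750 = 9.7. The null of no change is all but rejected before the study starts.

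**Step 2: power of the subset test when PaCO₂ has no effect.** If ΔK is unrelated to PaCO₂, the subset has the same mean μ and SD σ as the cohort. Power = P(|T| > t₀.₉₇₅,ₙ₋₁), where T is noncentral t with n − 1 df and noncentrality (μ/σ)√n. For μ = 0.73 and n = 10 the noncentrality is 1.377 × 3.162 = 4.36.

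| Subset n | rise 0.73 | rise 0.5 | rise 0.25 (illustrative) |
|---|---|---|---|
| 10 | 97.1% | 75.7% | 26.7% |
| 15 | 99.9% | 92.4% | 39.8% |
| 20 | 99.99% | 97.9% | 51.7% |
| 30 | >99.99% | 99.9% | 70.5% |

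Even a common rise of 0.25, half the design difference, gives 90.5% at n = 50 and 98.1% at n = 75.

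**Step 3: subset test against a real contrast.** 20,000 simulated studies of 150 patients per setting, ΔK independent of PaCO₂, SD 0.53. Only the share at or above 50 mmHg has to be assumed, not the mean or SD of PaCO₂. Percentage with p < 0.05, for a rise of 0.73 / 0.5:

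| Share ≥ 50 | paired test, ≥ 50 | paired test, < 50 | ≥ 50 vs < 50 | ΔK against PaCO₂ |
|---|---|---|---|---|
| 30% | 100 / 100 | 100 / 100 | 5.0 / 5.1 | 4.9 / 5.0 |
| 50% | 100 / 100 | 100 / 100 | 4.9 / 5.4 | 5.0 / 5.0 |
| 70% | 100 / 100 | 100 / 99.99 | 4.8 / 5.2 | 5.2 / 4.8 |
| 90% | 100 / 100 | 98.9 / 89.9 | 5.3 / 5.0 | 4.9 / 4.9 |

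The group below 50 mmHg is significant nearly as often, so significance at ≥ 50 does not discriminate. The contrast and the correlation hold their nominal 5%.

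**Step 4: what a contrast could detect.** At 80% power, difference = (1.96 + 0.8416) × 0.53 × √(1/n₁ + 1/n₂):

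- 75/75: 1.485 × 0.163 = 0.24 mmol/L
- 120/30: 1.485 × 0.204 = 0.30 mmol/L
- 135/15: 1.485 × 0.272 = 0.40 mmol/L

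For a correlation at n = 150: r = tanh(2.8016/√147) = 0.227. In an unadjusted slope that is 0.227 × 0.53 = 0.12 mmol/L per SD of ΔPaCO₂.

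**The case against.** **PaCO₂ is tested elsewhere.** A reader might infer that the respiratory attribution rests wholly on the two sensitivity analyses. It does not. The abstract lists the regression and the PaCO₂ correlation among the key secondary outcomes, and the Discussion names the association with severity of respiratory acidosis as a second line of argument. This stands and limits the consequence. It does not repair the purpose given to the ≥ 50 mmHg analysis: ΔPaCO₂ may be dropped from the regression at variable selection, and the confirming role is assigned elsewhere.

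**The base-excess exclusion can fail.** A reader might extend the criticism and say that this re-analysis is also bound to succeed. The documents do not support that. Its stated purpose is to assess the influence of metabolic acidosis. If the rise were concentrated in patients below −5 mmol/L, removing them would shrink the mean. It is a legitimate check of one rival explanation, and the calculations above do not cover it. What remains is wording: milder metabolic acidosis stays in the data, so the re-analysis neither controls for metabolic acidosis nor isolates a respiratory effect.

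**The test is inferred.** The paired t-test is named only for the base-excess exclusion. True, but any test of change within the ≥ 50 mmHg subset has the same null and the same flaw.

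**The subset mean could be compared with the full-cohort mean.** No such comparison is stated, and it would be weak. The subset mean exceeds the cohort mean by (1 − share) × (difference between ≥ 50 and < 50). With 90% in the subset and a true difference of 0.40 mmol/L, that is 0.1 × 0.40 = 0.04 mmol/L.

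**Conclusion.** The point holds. The ≥ 50 mmHg analysis cannot do what its purpose clause claims. If PaCO₂ has no effect on potassium, it is still significant with 97.1% probability at n = 10 and 99.99% at n = 20, given the preliminary mean and SD, and in 100% of simulated studies when 30% to 90% of 150 patients qualify.

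These figures rest on the preliminary 0.73 and 0.53 carrying over and on the assumed share. Significance is near-certain rather than guaranteed: with 10 patients and a rise of 0.5 the probability is 75.7%.

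It would go too far to conclude that the protocol has no test of PaCO₂ or that both sensitivity analyses are empty. The severity is moderate: the primary estimate, its test, the sample and the data collection are unaffected.

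**What to change.** 1. In Secondary outcomes, Sensitivity Analysis, relabel the ≥ 50 mmHg result as descriptive and remove the confirming purpose.
2. Report mean ΔK for PaCO₂ ≥ 50 and < 50 mmHg, with the difference and its 95% CI.
3. In the planned linear regression of ΔK, make ΔPaCO₂ a mandatory term together with a metabolic term (ΔBE or ΔLactate, chosen now). Base the PaCO₂ inference on the ΔPaCO₂ slope with its 95% CI, described as an association that remains open to confounding.
4. Report the base-excess exclusion as the change in the mean ΔK estimate with its CI, not as a fresh p-value against zero.
5. In the Discussion, replace the two claims about controlling for metabolic acidosis and isolating respiratory effects with a statement that the exclusion checks robustness to severe metabolic acidosis only.

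All variables are already on the data collection list, so the cost is analysis wording. One drawback: if few patients fall below 50 mmHg, the contrast in item 2 is imprecise (about 0.40 mmol/L detectable at 135/15), so the slope should lead. For the same reason, a predicted ΔK at no change in PaCO₂ may be extrapolation and should not be relied on.
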